## Methods

### Overall design

The intervention mixed methods design involves a stepped-wedge cluster randomized controlled trial testing the outcomes of training in recovery-oriented practice, together with an embedded qualitative study to identify the contextual enablers and challenges to implementing recovery-oriented practice within primary care settings. Eighteen general practices and community health centers were randomly allocated to one of two steps (9 months apart) to start an intervention comprising general practitioner training in the delivery of recovery-oriented practice. Data collection consists of cross-sectional surveys collected from patients of participating general practitioners at three time points: baseline, and again at the end of Steps 1 and 2 (see Fig. 1). A mixed methods design was chosen for a number of reasons, including that it would produce richer and more complete findings than that based on either the qualitative or quantitative approach alone. Combining these approaches can further explain and enhance the integrity of the project outcomes, so that a mixed methods design may assist with project credibility, particularly when multiple stakeholders are involved such as in the PULSAR project [28]. The use of qualitative and quantitative methods were integrated at different stages of the intervention trial [27]. Initially, qualitative methods were used in an exploratory manner to identify potential barriers to recovery-oriented training within primary care settings, and to inform the intervention design. Subsequently, quantitative methods are being used to then measure the effectiveness of the intervention. Following the intervention trial, qualitative methods will be used in an explanatory manner to gain a more nuanced understanding of GP experiences of implementing recovery-oriented practices and patient experiences of these practices [28]. Quantitative and qualitative data are collected from patient participants, but only qualitative data are collected from GP participants.

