#### Adaptations to design

Delays in recruitment of GPs and patients and in delivery of the intervention required some modification to the design in order to be able to deliver the project outcomes within the allowed project duration. Cluster definition was broadened to include one or more GPs from each site in an effort to boost recruitment. As well, study steps were reduced from 12 months to 9 months. Based on the Kirkpatrick training evaluation model [43], the 9-month step period is an acceptable time point for the measurement of change. It allows 3 months for consolidation and a 6-month period for patients to be exposed to GPs implementing recovery-oriented practice.

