
## Statistical analyses

The recovery-oriented practice training intervention for primary care will be evaluated at the patient level by examining the surveys of adult patients who consult the participating GPs for mental health issues. The main evaluation plan is to examine the cross-sectional surveys returned by patients during three data collection periods: baseline, Step 1, and Step 2 (see Fig. 1).

The planned data collection schedule depends on the training intervention being delivered at each cluster in the scheduled month (see Fig. 1). As training delays in some clusters are expected, the following two main analysis approaches are planned to compare the post-intervention and control (pre-intervention) periods:Study planned dataset, which will use data collected from patients during the planned six-month periods centered on the midpoints of February 2015, August 2015 and November 2015 (see Fig. 1). Other data collected outside of these timespans are considered a protocol violation and are excluded from this dataset.Per-protocol all data dataset, which will use all available data time-stamped from date of intervention received at the cluster, as outlined in Table 3.

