Time since intervention	All patient surveys are time-stamped in relation to the time the intervention was received at the cluster. Time value of “0” is given for the plus/minus three months from date of training; “1” for four-to-six months post training; “2” for seven-to-nine months post training, etc. Time value of “-1” for four-to-six months before training; “-2” for seven-to-nine months before training, etc.
Time	Study month that survey was completed: “0” = December 2014, “1” = January 2015, etc.
*Cluster level stratification variables*	
Clinic type	Privately owned general practice vs community health center.
GP clinic size	GP equivalent full time (EFT) size greater than 5 (yes/no).
Clinic location	Local government area location: Dandenong, Casey, Cardinia, other.
Specialist focus clinic	A specialist focus clinic (yes/no) was determined by more than 10% of the practice patients belonging to any of the following groups: a. people with HIV/AIDS b. people with enduring and serious mental illness (e.g., schizophrenia, bipolar disorder) c. people with permanent physical disabilities d. people with addictions e. homeless people f. transient/seasonal populations g. people living in poverty h. Aboriginal peoples i. recent immigrants (six months or less) j. people from cultural minorities k. people with sports injuries l. other

The primary analysis will examine the patient-level QPR scores (continuous data) at baseline, nine months (Step 1), and 18 months (Step 2), using a linear mixed-effects model. The model will include intervention status and time as fixed effects and clusters and patients as random effects. Both univariate and multivariable models will be developed based on baseline patient and cluster-level variables considered statistically significant (*p <* 0.10) or clinically important (e.g., age, sex), see Table 2, and included in the model as fixed. This will include the intervention dosage variable described earlier. Model fit will be examined by comparing AIC values.

Secondary analyses will examine the patient-level data of the INSPIRE, WEMWBS, and K10. Similar to the primary analysis, we will use linear mixed-effects models to compare the intervention and control periods (pre-intervention) for continuous outcomes and generalized linear mixed-effects models for binary outcomes.

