### Data collection and management

Table 3 outlines the data collected at each time point for participating GPs and patients. Patient participant data is being collected by the returned paper surveys or online surveys at three time points: baseline (months 4–6), Step 1 (months 16–18) and Step 2 (months 28–30), as displayed in Fig. 1. Both modes of survey completion are provided to offer flexible participation options. The estimated completion time for each round of surveys is approximately 45 min.

**Table 3 Tab3:** Schedule of enrolment, interventions, and assessments

	Time points			
Project events		T0	T1	T2
Intervention adaptation	X			
GP enrolment				
Eligibility screen	X			
Informed consent	X			
Randomization	X			
GP training intervention				
Year 1 clusters		X		
Year 2 clusters			X	
GP PALS				
Year 1 clusters		X	X	X
Year 2 clusters			X	X
Patient recruitment				
Eligibility screen by GP		X	X	X
Survey packs provided to eligible patients via GPs		X	X	X
Informed consent		X	X	X
Patient quantitative assessment				
Demographics		X	X	X
QPR		X	X	X
WEMWBS		X	X	X
INSPIRE		X	X	X
K10		X	X	X
Health economic items		X	X	X
GUPI		X	X	X
GP qualitative assessment				
Informed consent			X	X
Individual interview			X	
Individual interview/focus group				X
Patient qualitative assessment				
Informed consent			X	X
Individual interview			X	
Individual interview/focus group				X

The online survey option collects participant-entered data directly from Qualtrics online survey software. Qualtrics securely collects participant responses within a secure back-end spreadsheet that is only accessible by the researchers via password protected files.

If patient participants consent to allowing the researchers to access their routinely collected medical records, additional information will be extracted from these files with the assistance of the participating GP/s in each cluster site, including information about diagnosis and mental health status and medication details relating to mental health issues.

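### The survey windows defining the study planned dataset fall at 0, 6 and 9 months, not the 0, 9 and 18 months of the design; two overlap by half and an 18-month round is excluded

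*Protocol article*

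**What the plan says.** All references are to the protocol article.

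- **Statistical analyses** names two datasets for comparing post-intervention with control periods. The study planned dataset uses surveys from "six-month periods centered on the midpoints of February 2015, August 2015 and November 2015", and adds: "Other data collected outside of these timespans are considered a protocol violation and are excluded from this dataset". The second dataset takes all available surveys, timed from the actual training date at each cluster.
- **Overall design** has clusters "randomly allocated to one of two steps (9 months apart". **Adaptations to design** says that "study steps were reduced from 12 months to 9 months" and explains the new length: "It allows 3 months for consolidation and a 6-month period for patients to be exposed".
- **Main analysis plan** takes the primary outcome as "QPR scores (continuous data) at baseline, nine months (Step 1), and 18 months (Step 2".
- **Data collection and management** places the rounds at "baseline (months 4–6), Step 1 (months 16–18) and Step 2 (months 28–30".
- The **Fig. 1** legend gives each of the three rounds a six-month collection period. The figure itself is not shown in the text available for this review.

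**The concern.** The window rule decides which surveys enter the study planned dataset and which round they belong to. In a stepped-wedge trial the round carries the time effect and, with the cluster's allocation, the planned exposure. If the window dates do not match the design, the dataset is not the one that the primary analysis describes.

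Two consequences follow from the printed dates. Some surveys fall in two rounds with no rule to separate them. The final round falls in none, and the plan calls its surveys protocol violations. If this is left open, the windows would have to be settled after the data are in hand.

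**Working it through.** **Inputs.** Window centres mid-February, mid-August and mid-November 2015, each window six months wide, so centre ± 3 months (Statistical analyses). Steps of nine months (Overall design; Adaptations to design). Analysis at 0, 9 and 18 months (Main analysis plan). Rounds at months 4–6, 16–18 and 28–30 (Data collection and management). Study month 0 is December 2014 (Table 2).

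**Step 1: spacing of the printed centres.** February to August 2015 is 6 months and February to November 2015 is 9 months. The printed set is 0, 6, 9. The 0, 9, 18 of the Main analysis plan is not reproduced.

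**Step 2: printed windows against nine-month steps from the printed baseline.**

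| Round | Printed window | Window on nine-month steps |
|---|---|---|
| Baseline | mid-Nov 2014 to mid-May 2015 | mid-Nov 2014 to mid-May 2015 |
| Step 1 | mid-May to mid-Nov 2015 | mid-Aug 2015 to mid-Feb 2016 |
| Step 2 | mid-Aug 2015 to mid-Feb 2016 | mid-May to mid-Nov 2016 |

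The window printed third is the one that the nine-month timetable gives to Step 1. The window printed second matches no round of that timetable.

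**Step 3: overlap.** The second printed window, 15 May to 15 November 2015, has 184 days. It shares 15 August to 15 November 2015 with the third, which is 92 days; 92 / 184 = 50%. The first and second windows touch without a gap. On nine-month steps the overlap is zero and the gaps are 9 − 6 = 3 months.

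**Step 4: the 18-month round.** February 2015 + 18 months = August 2016, window mid-May to mid-November 2016. The last printed window closes in mid-February 2016, three months before this one opens. The overlap with each printed window is 0 months.

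**Step 5: other readings.**
- Take November 2015 as month 18 and count back. Baseline becomes May 2014, which contradicts the printed February 2015 and precedes study month 0.
- Use the months in Data collection and management. Their midpoints are 5, 17 and 29, so rounds are 12 months apart and three months long. Anchored at February 2015, the last round falls around February 2017, again outside every printed window.

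No reading places an 18-month round inside the printed windows.

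**Step 6: what losing the last round would cost in precision.** The Hussey–Hughes variance for I clusters and T periods is

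Var = I·s²·(s² + T·t²) / [(I·U − W)·s² + (U² + I·T·U − T·W − I·V)·t²],

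where s² = SD²(1 − ICC)/n and t² = SD²·ICC. U is the number of exposed cells, W the sum of squared column totals of the exposure matrix, and V the sum of squared row totals. SD 16, ICC 0.05 and 18 clusters are from the article. Ten patients per cluster-period and nine clusters per step are assumptions. Then s² = 256 × 0.95 / 10 = 24.32 and t² = 256 × 0.05 = 12.8.

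- Three rounds (U = 27, W = 405, V = 45): 18 × 24.32 × 62.72 / (81 × 24.32 + 162 × 12.8) = 6.79, SE 2.606.
- First two rounds only (U = 9, W = 81, V = 9): 18 × 24.32 × 49.92 / (81 × 24.32 + 81 × 12.8) = 7.27, SE 2.696.

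The SE rises by 3.5%. The difference detectable with 80% power goes from 7.30 to 7.55 QPR points. With 30 GPs × 10 / 18 = 16.7 patients per cluster-period the rise is 5.5%.

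**The case against.** The strongest reply is that this is a slip in a condensed article, probably August 2015 printed for August 2016 and out of order, and that any reader sees 0, 9 and 18 months elsewhere. That is a plausible cause. It does not make the point clerical, because the affected sentence is the inclusion rule of a main dataset, and the third timetable means that the article cannot be used to correct itself. Without Fig. 1 the intended dates remain an inference, and that part of the reply stands.

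The reply also stands against several stronger conclusions that a reader might draw:

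- *Surveys are counted twice.* The rule says which surveys are used. A survey inside two windows is still one record, and Table 2 gives it a single completion month. Only its round is ambiguous.
- *The effect estimate is attenuated by a known amount.* This needs exposure coded by window label. The Abstract does speak of analysis by assigned group at each time point, but Table 2 defines intervention status by whether a six-month lag has passed, and untrained clusters would then be coded 0. The article does not settle which applies, and any figure would also depend on an assumed exposure of the early clusters in the second window.
- *A third of the trial's surveys is lost.* That assumes every GP meets the target in every round, although the article reports sites short of their baseline target. The exclusion also applies to one dataset only.
- *A post-training window opening in mid-May 2015 was impossible, because randomization ran to June 2015.* The article does not say that any late-randomized cluster went to Step 1.
- *The months in Data collection and management belong to the superseded design.* The 12-month spacing equals the former step length, but the article does not say so, and the text stands as current.

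**Conclusion.** The contradiction holds on the text alone. The windows of the study planned dataset are inconsistent with the plan's own step length and analysis times, half of the second window is also in the third, and an 18-month round has no window. As written, the dataset lacks the round in which later-trained clusters contribute post-intervention surveys, and the definition of a round fails for three months of 2015.

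The harm is to period assignment and to the stepped-wedge comparison. The loss of nominal precision is small, an SE 3.5% to 5.5% larger under the assumptions in the working. The all-data dataset limits the damage, but both datasets are presented as main approaches, so it does not remove the error.

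The contradiction rests on no assumption about Fig. 1. The replacement dates do: they take the printed February 2015 baseline and nine-month steps as intended. A last round in 2016 fits the project period of 2013 to 2017.

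**What to change.** 1. Reconcile the window dates in Statistical analyses, the times in Main analysis plan and the months in Data collection and management with Fig. 1.
2. Restate the windows as non-overlapping six-month periods on the nine-month spacing. From the printed baseline the midpoints are February 2015, November 2015 and August 2016, subject to the sponsor's confirmation against Fig. 1.
3. Add one sentence saying that each survey is assigned to exactly one period.

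The cost is corrected dates in two sections and one added sentence. No new data are needed. The correction should be fixed and dated before outcomes are compared by period.

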### Main analysis plan

Descriptive statistics will be used to summarize the characteristics of the patient-level variables and the GP clinics (clusters), see Table 2. Cluster-level variables are those used in the stratified randomization, which are four types of organizational variations, plus the intervention status of the cluster and the time since (or before) the intervention. The intraclass correlation coefficient (ICC) will be calculated and reported.

**Table 2 Tab2:** Individual and cluster-level variables available for multivariable analysis

Variable	Description
*Individual level*	
Demographics	
Sex	Sex of patient.
Age	Age of patient at survey completion date.
Country of birth	Country of birth of patient.
Ethnicity	Ethnic or cultural group that the patient identifies with.
Main language	Main language spoken at home.
Marital Status	Marital status of patient.
Living situation	Current living situation of patient.
Education	Education level of the patient.
Health Economics	
Mental health medications	Medications for mental health taken regularly by the patient.
Employment	Current working status of the patient.
Income	Usual weekly income of patient, after tax, from all sources of employment.
Days out of role	Number of days in the past month that the patient was totally or partly unable to carry out normal activities because of mental health problems.
Days absent from work	Number of days in the past month that the patient was absent from work due to illness or disability, and due to mental health problems.
Hospitalizations	Number of hospital admissions for physical problems and for mental health problems, including number of nights in total and reasons for most recent admissions.
Consultations with health professionals	Number and length of consultations with health professionals for physical health and mental health problems.
GUPI	The General-Practice Users’ Perceived-need Inventory is a one-page instrument developed to assess participants’ estimation of their needs for mental health care and the meeting of those needs.
*Cluster level*	
Cluster group	Allocated to receive the intervention at either Step 1 or Step 2.
Intervention status (0/1)	A lag time of six months is anticipated until intervention effects are possible. The intervention status variable indicates that this lag time has passed.
Dosage (%)	Intervention dosage.
Time since intervention	All patient surveys are time-stamped in relation to the time the intervention was received at the cluster. Time value of “0” is given for the plus/minus three months from date of training; “1” for four-to-six months post training; “2” for seven-to-nine months post training, etc. Time value of “-1” for four-to-six months before training; “-2” for seven-to-nine months before training, etc.
Time	Study month that survey was completed: “0” = December 2014, “1” = January 2015, etc.
*Cluster level stratification variables*	
Clinic type	Privately owned general practice vs community health center.
GP clinic size	GP equivalent full time (EFT) size greater than 5 (yes/no).
Clinic location	Local government area location: Dandenong, Casey, Cardinia, other.
Specialist focus clinic	A specialist focus clinic (yes/no) was determined by more than 10% of the practice patients belonging to any of the following groups: a. people with HIV/AIDS b. people with enduring and serious mental illness (e.g., schizophrenia, bipolar disorder) c. people with permanent physical disabilities d. people with addictions e. homeless people f. transient/seasonal populations g. people living in poverty h. Aboriginal peoples i. recent immigrants (six months or less) j. people from cultural minorities k. people with sports injuries l. other

The primary analysis will examine the patient-level QPR scores (continuous data) at baseline, nine months (Step 1), and 18 months (Step 2), using a linear mixed-effects model. The model will include intervention status and time as fixed effects and clusters and patients as random effects. Both univariate and multivariable models will be developed based on baseline patient and cluster-level variables considered statistically significant (*p <* 0.10) or clinically important (e.g., age, sex), see Table 2, and included in the model as fixed. This will include the intervention dosage variable described earlier. Model fit will be examined by comparing AIC values.

Secondary analyses will examine the patient-level data of the INSPIRE, WEMWBS, and K10. Similar to the primary analysis, we will use linear mixed-effects models to compare the intervention and control periods (pre-intervention) for continuous outcomes and generalized linear mixed-effects models for binary outcomes.

Estimated intervention effects will be reported as the mean outcome difference for continuous outcomes and Odds Ratio for binary outcomes between intervention and control periods, assuming a constant treatment effect over time. This can be described as a meta-analysis approach as (in the case of continuous data) the mean change in each cluster will be standardized by using the variance of the outcome measure within that cluster. The estimated intervention effects will be reported with 95% Confidence Intervals and *p* values. Analysis will be conducted using Stata V.14, StataCorp. Stata Statistical Software: Release 14. College Station, TX: StataCorp LP, 2015.

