#### Sample size targets

The study has two sample groups: GPs and patients of these GPs. Sample size calculations were done using Stata statistical software *stepped-wedge*: for clusters defined at the level of the general practice site, the primary outcome measure is the QPR, with a published mean of 46 and standard deviation of 16, power of 0.80, significance level set at 0.05, intraclass correlation coefficient (ICC) within practice sites of 0.05, the number of steps (2), and patient data collected cross-sectionally at three time points (baseline, Step 1, and Step 2).

The original sample target was a minimum of 20 different sites (clusters) with one GP per site; each GP was required to recruit a minimum of 30 patients during the four-year project (10 patients at baseline, 10 at Step 1, and 10 at Step 2), resulting in a minimum of 600 patient participants overall.

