#### Adaptations to sample size targets

Challenges in engaging GPs and recruiting patients were encountered at the beginning of the project (see earlier and also below). As a result, the protocol was adapted so that more than one GP from each cluster can participate. Each participating GP is still expected to recruit a minimum of 30 patients over the duration of the trial; therefore, if there are two participating GPs at a cluster, each will recruit 30 patients, resulting in 60 patients for that cluster. This efficiency of scale appears to be working well in some clusters. The required cluster number was also reduced from 20 to 10 plus. These sample numbers will be sufficient to detect a medium to medium-large effect in the primary outcome.

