### Sensitivity analyses

A missing data analysis will investigate any patterns of missingness. For each primary and secondary outcome component with missing data, multiple imputation using multivariate regression with factors of age, gender, time, and intervention status will produce 100 estimates. Sensitivity analyses will be performed using this multiple imputation to account for missing data and then re-running the analyses.

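### The primary model's patient random effect is redundant for cross-sectional surveys, and with no cluster-by-period effect the standard error is understated if within-practice correlation falls between rounds

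*Protocol article*

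**What the plan says.** The Main analysis plan specifies a linear mixed-effects model for QPR at baseline, Step 1 and Step 2: "The model will include intervention status and time as fixed effects and clusters and patients as random effects". No cluster-by-period term is named.

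The sampling is described as cross-sectional in three places:
- Overall design: "Data collection consists of cross-sectional surveys collected from patients of participating general practitioners at three time points".
- Statistical analyses: "The main evaluation plan is to examine the cross-sectional surveys returned by patients during three data collection periods".
- Sample size targets: "the number of steps (2), and patient data collected cross-sectionally at three time points". Each GP recruits "10 patients at baseline, 10 at Step 1, and 10 at Step 2", "resulting in a minimum of 600 patient participants overall". Since 20 sites × 30 = 600, every survey is counted as a separate patient. One within-site ICC of 0.05 is used, with no between-period value.

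Under Adaptations to sample size targets, "the protocol was adapted so that more than one GP from each cluster can participate", and the required number of clusters falls from 20 to 10 or more. For missing data, the Sensitivity analyses section states that "multiple imputation using multivariate regression with factors of age, gender, time, and intervention status will produce 100 estimates". Cluster is not among these factors.

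**The concern.** A patient random intercept belongs to a design that measures the same people repeatedly. In a repeated cross-section it has nothing to estimate. The dependence that such a design can have is a shift shared by all patients of one practice in one round, and the stated model leaves this out.

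The training effect is estimated largely from changes within practices between rounds, so variation of that kind feeds directly into its error. A model with one cluster intercept treats two patients of a practice as equally correlated whether they were surveyed in the same round or in different rounds. If that is untrue, the confidence interval for the primary outcome is too narrow and the test rejects too often.

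The article gives grounds to expect such shifts. Recruitment methods vary by practice. Baseline recruitment took one week at one site and was unfinished after six months at others. The base site payment rose from $200 to $500. The dosage variable allows for trained staff leaving.

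**Working it through.** **Inputs**
- SD 16, ICC 0.05, power 0.80, significance level 0.05 (Sample size targets; two-sided is assumed). Total variance is 16² = 256, of which 0.05 × 256 = 12.8 is between practices and 243.2 is not.
- 18 sites (Overall design) and 30 GPs (Adaptations to GP recruitment and retention). At 10 patients per GP per round, this is 30 × 10 / 18 = 16.7 per site-round.
- 10 sites (revised minimum), here with 20 patients per site-round, that is, two GPs per site (assumed).
- Between-period autocorrelation r of the practice effect: not in the documents, so it is varied.

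**1. The patient term.** With one survey per patient, an observation has variance 12.8 + patient variance + residual variance, and two patients of a practice have covariance 12.8. Only the sum of the last two variances enters the likelihood. On one simulated data set (18 sites, 10 per site-round), splitting 243.2 as 0/243.2, 100/143.2, 200/43.2 or 240/3.2 gave the same REML log-likelihood (−1759.139), estimate (0.639) and SE (2.606) each time. The split is not identifiable, and it does not move the interval.

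**2. SE formula.** Take I sites, half on sequence 0-1-1 and half on 0-0-1, period as a category, and m patients per site-round. Let s² = 243.2/m + (1 − r) × 12.8 and c = r × 12.8. The generalized least squares variance of the training effect is then

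Var = (4/I) × s²(s² + 3c)/(s² + 2c).

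**3. The plan's own design.** With I = 20, m = 10, r = 1: s² = 24.32 and c = 12.8. Var = 0.2 × 24.32 × 62.72/49.92 = 6.11, so SE = 2.47. The difference detectable with 80% power is 2.80 × 2.47 = 6.93 QPR points, or 0.43 SD. The plan states no target difference, so its power cannot be reproduced exactly. This value is broadly compatible with its verbal claim of a medium to medium-large effect.

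**4. SE when the correlation decays**

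| Design | r | s² | c | SE | Ratio to r = 1 |
|---|---|---|---|---|---|
| 18 × 16.7 | 1 | 14.59 | 12.80 | 2.07 | 1 |
| 18 × 16.7 | 0.95 | 15.23 | 12.16 | 2.10 | 1.02 |
| 18 × 16.7 | 0.8 | 17.15 | 10.24 | 2.20 | 1.07 |
| 18 × 16.7 | 0.6 | 19.71 | 7.68 | 2.31 | 1.12 |
| 18 × 16.7 | 0.5 | 20.99 | 6.40 | 2.36 | 1.14 |
| 10 × 20 | 1 | 12.16 | 12.80 | 2.55 | 1 |
| 10 × 20 | 0.8 | 14.72 | 10.24 | 2.76 | 1.08 |
| 10 × 20 | 0.5 | 18.56 | 6.40 | 2.99 | 1.17 |

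With 18 × 16.7, power at the difference that the cluster-only calculation detects with 80% falls to 75% at r = 0.8 and 69% at r = 0.5.

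**5. Type I error of the cluster-only model** (simulation under no effect, REML, z test, 1,500 to 2,000 trials per setting, Monte Carlo error about 0.5 points)
- 18 equal sites of 17: 6.5% at r = 1, 6.3% at 0.8, 9.1% at 0.5. At r = 0.5 the mean model SE was 2.01 against a true SD of 2.35.
- 30 GPs in 18 sites, equal sites: 5.5% at r = 1, 7.5% at 0.8, 9.8% at 0.6.
- 30 GPs in 18 sites, 1 to 4 per site (assumed spread), two separate runs: 5.7% and 4.4% at r = 1, 7.5% and 8.0% at 0.8, 10.9% and 9.6% at 0.6.
- 10 sites of 20: 5.4% at r = 1, 9.3% at 0.8, 12.3% at 0.5.

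**6. With a cluster-by-period effect added.** 18 sites of 17: 5.0% at r = 0.8 and 5.5% at 0.5. 10 sites of 20: 6.2% and 7.3%.

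**The case against.** The strongest objection is that the understatement is conditional. The documents give one ICC and no between-period value, and at r = 1 the stated model is adequate. The Statistical analyses section centres the rounds on February, August and November 2015, six and three months apart, which favours a high autocorrelation. At 0.95 the SE changes by only about 2%. One simulation also gave 6.3% at r = 0.8 against 6.5% at r = 1, so at mild decay the excess is hard to tell from Monte Carlo error. All of this stands, and it is why the size is given as a range.

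Repeat response is not barred. The article speaks of retention and of improvements from pre- to post-intervention, and it stores data in re-identifiable form. If repeat responders were linked, a patient effect would be estimable. That stands as an exception, but the sample size counts every survey as a different patient.

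Three stronger readings might be inferred, and none is supported:
- That the patient term narrows the interval. Step 1 shows that it does not.
- That the missing GP level narrows it. A lasting GP effect largely cancels from between-round contrasts. Adding a GP variance of 6.4 or 12.8 gave a true SE of 2.077 or 2.080 against 2.074 from the cluster-only model.
- That the imputation model affects the primary result. It is confined to a sensitivity analysis.

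It could also be said that a condensed article leaves such detail to the full plan. Here, however, the random effects are stated. The meta-analytic description that follows standardizes by within-cluster variance and does not supply a cluster-by-period component.

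**Conclusion.** The concern holds in a limited form. The stated random effects do not fit a repeated cross-section: one is redundant, and the one that such a design may need is absent. The redundancy is a matter of specification and convergence, not of precision.

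The missing term matters only if r is below 1. A reader might infer that the interval is certainly too narrow, but the documents contain no figure that would show this. With ICC 0.05 and 18 sites of about 17 per round, the understatement is small at r = 0.95 and moderate at 0.8 to 0.5, where type I error is about 6 to 11% in place of 5%. The 10-site minimum is more exposed. These figures assume full recruitment of 10 patients per GP per round, and some also assume a spread of GPs across sites that the article does not report.

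**What to change.** In the Main analysis plan, replace the patient random effect with a cluster-by-period random effect, period being the data-collection round, and keep the cluster effect. Retain a patient effect only if repeat responders are identified and linked, and say so. A GP-within-site effect is optional.

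The change is one of wording. If the correlation decays, the interval at 18 sites is up to about 14% wider. If it does not, little changes: in simulation at r = 1 with 18 sites of 17, the mean SE went from 2.03 to 2.11, about 4%. Near 10 sites the added term does not fully restore 5%, so a small-sample correction should accompany it. Power should be reported over a range of autocorrelations.

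As a secondary change, include cluster in the imputation model of the sensitivity analysis, so that imputed scores carry the practice effect that the analysis model assumes.
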